### Primary outcome

The primary outcome is OM severity, graded via the WHO scale [ 31], comparing TC versus IO PBMT groups in patients undergoing RT or CRT. Comparative analyses will be performed between transcutaneous and intraoral PBMT groups.

### Secondary outcomes

Compare IO and TC PBMT regarding:

OM severity (NCI-CTCAE);Pain intensity (NRS);Ulcerated area extension (grades 2–4) will be registered with digital images;Treatment interruptions (unplanned RT/CRT modifications);Unscheduled healthcare utilization (emergency visits or hospitalizations due to OM complications).

This study explores PBMT delivery routes to standardize application parameters and optimize supportive care for patients with head and neck malignancies.

### Statistical analysis

Analyses will be performed using Jamovi software (version 2.6.44). Normality will be assessed using the Shapiro-Wilk test, and variables will be described using frequencies and percentages (categorical variables) or means, standard deviations, and medians with interquartile ranges (continuous variables). Baseline comparability between groups will be assessed using Student’s t-test or the Mann-Whitney U test (continuous variables) and the chi-square test or Fisher’s exact test (categorical variables).

The primary outcome, oral mucositis severity (WHO scale), will be analyzed longitudinally using a mixed-effects ordinal logistic regression model to account for the repeated measurements. The model will include treatment group, assessment time, and the treatment vs. time interaction as fixed effects, with participant included as a random effect to account for within-subject correlation. Total radiotherapy dose, tumor location, and concomitant chemotherapy will be included as covariates.

Pain intensity (NRS) will be analyzed longitudinally using an appropriate mixed-effects regression model according to its distribution. The primary analysis will follow the intention-to-treat principle. Missing outcome data will not be imputed; instead, the mixed-effects ordinal logistic regression model will incorporate all available repeated measurements and account for incomplete observations over time under the assumption that data are missing at random.

The primary objective is to determine whether transcutaneous infrared PBMT is non-inferior to intraoral red PBMT regarding oral mucositis severity. Non-inferiority will be assessed using the estimated treatment effect obtained from the longitudinal mixed-effects model and interpreted according to the prespecified non-inferiority margin of 0.5 WHO grade.

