## Sample size

The sample size was determined based on a non-inferiority design, assuming that transcutaneous infrared PBMT would demonstrate clinical efficacy comparable to intraoral red PBMT in the prevention of OM. The non-inferiority margin was defined as Δ = 0.5 points on the WHO scale, based on the differences observed between CT and IO protocols in direct comparative studies [25, 26]. Calculations were performed using the ClinCalc platform to compare two independent means, assuming a significance level (α) of 0.025 (one-tailed test) and a statistical power (1 - β) of 80%. To account for a predicted 10% attrition rate (dropouts), the final sample size was established at 54 participants (*n* = 27 per group). Participants will be recruited through consecutive sampling to ensure a representative flow of patients at the study site.

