## Clinical and treatment-related variables

Prophylactic PBMT will be administered thrice weekly during radiation therapy. Following institutional standards, all patients will undergo intensity-modulated radiation therapy (IMRT). The prescribed radiation regimen consists of total doses ranging from 60 to 70 Gy, delivered in 30 to 35 fractions of 2 Gy (200 cGy) per fraction, five days a week.

Following a pragmatic design, patients on concurrent chemotherapy will be included. As chemotherapy significantly impacts OM risk, it will be recorded and treated as a covariate in multivariable regression analyses to adjust for potential confounding on outcomes.

The standardized PBMT schedule was set for Monday, Wednesday, and Friday during all weeks of RT, ensuring a maximum interval of two days between sessions and coverage of at least three consecutive RT fractions. Three times per week (rather than daily) was based on the operational feasibility of the referral oncology service (patient flow and researcher availability), evidence from randomized clinical trials demonstrating that the efficacy of three-times-weekly PBMT protocols is comparable to daily frequency in SCC populations [22], and protocols approved by the MASCC/ISOO guidelines that include alternate frequencies [17].

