## Discussion

Mucositis remains a common and debilitating complication of CRT in patients with head and neck cancer, associated with severe pain, worsening nutritional status, treatment interruptions, and a significant decline in quality of life, even with modern RT protocols and supportive care [22, 23, 33].

Recent systematic reviews and meta-analyses have established a high level of evidence confirming that PBMT effectively reduces the incidence, duration, and severity of OM, as well as associated pain, in the HNC population. These therapeutic effects typically manifest between the second and third weeks of RT and persist throughout the treatment course [23, 34]. Reflecting this robust evidence, the MASCC/ISOO clinical practice guidelines updated their recommendations to strongly favor the use of intraoral PBMT for the prevention of OM in patients undergoing either RT alone or concurrent CRT [17, 23, 35]. While the intraoral route is currently the clinical standard, the exploration of alternative delivery modalities such as transcutaneous application remains a critical frontier in optimizing patient comfort and clinical efficiency.

Evidence from clinical trials highlights that both daily and thrice-weekly prophylactic PBMT regimens significantly attenuate severe oropharyngeal pain and reduce the requirement for opioid and non-opioid analgesics [22, 33, 36, 37]. Beyond pain management, recent data by Hu et al. [38] have demonstrated that daily PBMT not only mitigates oropharyngeal discomfort but also results in a lower incidence of enteral feeding tube insertions. These findings suggest that PBMT plays a pivotal role in preserving nutritional autonomy and functional status, ultimately leading to superior health-related quality of life (HRQoL) during aggressive oncological treatment. By maintaining the integrity of the oral and oropharyngeal mucosa, PBMT facilitates the maintenance of oral intake, preventing the common trajectory of weight loss and dehydration associated with chemoradiotherapy [22, 33, 34, 36, 37, 38].

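### The effect judged against the 0.5-grade margin has no stated visit or window, and two direct readings of it favour non-inferiority

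*Protocol article*

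**What the plan says.** All references are to the protocol article.

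- **Visits.** Under Clinical and treatment-related variables, "The standardized PBMT schedule was set for Monday, Wednesday, and Friday during all weeks of RT". RT runs to 30–35 fractions at five per week. Data collection has participants evaluated clinically at each session, so WHO grading starts in week 1.
- **Model.** Statistical analysis plans a mixed-effects ordinal logistic regression with group, time and their interaction as fixed effects and participant as a random effect. In its sentence on missing data it adds that "the mixed-effects ordinal logistic regression model will incorporate all available repeated measurements".
- **Decision rule.** "Non-inferiority will be assessed using the estimated treatment effect obtained from the longitudinal mixed-effects model", and this effect is read against the margin. Neither this section nor Primary outcome names a visit, a window or a summary over time.
- **Margin.** Under Sample size, "The non-inferiority margin was defined as Δ = 0.5 points on the WHO scale", again with no time reference.
- **Timing of benefit.** The Discussion says of PBMT: "These therapeutic effects typically manifest between the second and third weeks of RT and persist throughout the treatment course".

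**The concern.** With a treatment-by-time interaction the TC minus IO difference may change from visit to visit. The estimated treatment effect is then not one number until someone says where on the time axis it is read. The choice matters because the early visits carry little information about the comparison: if PBMT effects appear only between weeks 2 and 3, the arms are expected to look alike before then, whatever their relative merit.

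In a superiority trial, visits that cannot show a difference cost power. In a non-inferiority trial they pull the estimate towards zero and help the claim. A rule that can be read at baseline, over the whole course or late in treatment could let the same data pass or fail. The trial is open-label and the treating team grades the outcome (Randomization and blinding), so the choice should be fixed before results are seen.

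**Working it through.** **1. The plan's own figure.** The design inputs are "assuming a significance level (α) of 0.025 (one-tailed test) and a statistical power (1 - β) of 80" per cent, a margin of 0.5, 10% attrition and 27 per group. No SD is given, so 54 cannot be reproduced from stated inputs. Working backwards, n per arm = 2 × [SD × (1.960 + 0.842) / 0.5]². An SD of 0.615 gives 23.8, so 24, and 24 / 0.9 = 26.7, so 27. SDs of about 0.61 to 0.618 all lead to 27. The steps below do not need the SD.

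**2. Visit counts.** 30 / 5 × 3 = 18 sessions over 6 weeks; 35 / 5 × 3 = 21 sessions over 7 weeks. Two quiet weeks hold 6 visits: 6/18 = 33% or 6/21 = 29%.

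**3. All-visit average in WHO grades.** Assume no difference for q quiet weeks, a constant deficit d afterwards and equal weight per visit. Over W weeks the average is d × (W − q) / W. An average of 0.5 therefore corresponds to d = 0.5 × W / (W − q):

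| Quiet weeks q | W = 6 | W = 7 |
|---|---|---|
| 1 | 0.60 | 0.58 |
| 2 | 0.75 | 0.70 |
| 3 | 1.00 | 0.875 |

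Two weeks is the central reading of the Discussion; one to three is the range taken around it.

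**4. Does this carry over to the planned type of model?** A population-level proportional-odds illustration was run without random effects. Its inputs are assumptions: cutpoints 0, 1.5, 3 and 5, and IO severity at location 1.0 in week 3, rising by 0.6 per week. In weeks 1–2 the location was either −6 (almost everyone at grade 0) or −1 (about 27% at grade 1 or above, since 1/(1 + e) = 0.27). The true deficit from week 3 was 0.75 (6 weeks) or 0.70 (7 weeks), with none before.

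| Weeks, early location | True later log-odds ratio | Fitted common log-odds ratio | All-visit difference in grades, common-effect model | Linear interaction: first visit | All-visit | Last visit |
|---|---|---|---|---|---|---|
| 6, −6 | 1.352 | 1.347 | 0.499 | 0.018 | 0.462 | 0.743 |
| 6, −1 | 1.352 | 1.025 | 0.475 | 0.021 | 0.481 | 0.824 |
| 7, −6 | 1.296 | 1.293 | 0.500 | 0.037 | 0.465 | 0.626 |
| 7, −1 | 1.296 | 1.031 | 0.480 | 0.056 | 0.480 | 0.705 |

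The last three columns are differences in mean WHO grade.

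- With time coded from the first visit, the group coefficient corresponds to only 0.02–0.06 grade, although the later deficit is 0.70–0.75.
- The all-visit difference is 0.46–0.50, at or just under the margin.
- The last visit gives 0.63–0.82, above the margin.
- A common log-odds ratio is hardly diluted when early visits are nearly all grade 0, but it is when some early grades are above 0.

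**5. Illustrative error rate, only if the margin is meant for the active weeks.** The planned SE follows from the design: 0.5 / (1.960 + 0.842) = 0.178. Let the true deficit from week 3 be exactly 0.5, and let f be the share of later visits, 12/18 or 15/21. The all-visit mean is then 0.5f, that is 0.33 or 0.36.

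- SE 0.178 taken for the later mean: Φ[(0.5 − 0.5f) / (0.178f) − 1.96] = 0.288 (6 weeks) or 0.201 (7 weeks).
- SE 0.178 taken for the all-visit mean: Φ[(0.5 − 0.5f) / 0.178 − 1.96] = 0.152 or 0.123.

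The nominal rate is 0.025.

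**The case against.** The strongest reply is that the protocol nowhere plans an average over visits. The words about using all repeated measurements concern missing data: they say what enters the model, not which contrast is judged. A reader might infer from them that the decision rests on a course average, but the documents do not say so. That stands, and the 0.70–0.75 figures hold only for that reading. A late-week contrast from the same model would not be diluted in this way.

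Three further points stand.

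- **Scale.** The dilution needs conversion to mean grades with equal visit weights. On the log-odds scale it can be almost absent.
- **Error rate.** A reader might take 12–29% as the trial's false-positive rate. That presumes the margin applies from week 3, which the protocol does not state. If the target is the course average, a later deficit of 0.5 is a true difference of 0.33–0.36, inside the margin, and concluding non-inferiority is no error.
- **Quiet period.** Two weeks is inferred, and the Discussion does not say that grades stay near 0 until week 3. The visit count also stops at the end of RT, although the article mentions follow-up visits.

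It may also be said that whole-course severity is a defensible target in a prevention trial, since the Discussion cites delayed onset as a benefit of the transcutaneous route. That is fair, and it is a reason to keep the all-visit result in view.

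One argument does not carry: that this is mere detail for an analysis plan. The article itself states the decision rule (data, model, effect and margin). As stated, the rule gives no single effect.

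**Conclusion.** The point holds in conditional form. The decision rule reads an unspecified effect from a model in which the effect may vary over time. Two direct readings, the baseline-referenced group coefficient and the equally weighted all-visit difference in grades, can pass a TC deficit above 0.5 grade in the weeks with mucositis.

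Under the all-visit reading, 0.5 corresponds to a later deficit of 0.70–0.75 grade with two quiet weeks, and 0.58–1.00 across one to three. This assumes no early difference, a constant later deficit and equal visit weights. Even the lowest value exceeds the margin. Under the baseline reading the illustration leaves 0.02–0.06 grade of a 0.70–0.75 deficit, given its assumed severity curve and time linear from the first visit.

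The 12–29% rates illustrate what follows if the margin is meant for the active weeks. They are not a property of the plan as written. The change should be made before analysis.

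**What to change.** Keep all visits and the interaction in the model. Add to Statistical analysis that the decision contrast is the model-based TC minus IO difference in mean WHO grade, averaged over a stated window in which an effect can appear. Week 3 to the planned end of RT is one example in line with the Discussion. Non-inferiority is concluded if the upper limit of the two-sided 95% confidence interval (one-sided 0.025) lies below 0.5. State that the 0.5 margin refers to this window, and check that the sample-size assumption does too. Report the all-visit average as supportive, so that any earlier-onset difference stays visible.

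The cost is a sentence or two of text and a somewhat wider interval than the all-visit average would give.

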## Randomization and blinding

Participants will be randomized (1:1) to TC or IO groups via Random.org (*n* = 54). The research team will perform sequential, simple randomization without blocks or stratification. Due to the distinct application methods and wavelengths (red vs. infrared), double-blinding is unfeasible. Moreover, outcome assessors responsible for WHO and NCI-CTCAE oral mucositis grading cannot be blinded, as the clinical team involved in treatment delivery will also perform the evaluations. Therefore, this is an open-label trial, and the lack of blinding represents a potential limitation of the study. To minimize potential detection bias, examiners will undergo calibration before study initiation, standardized assessment criteria will be applied, and photographic documentation will support mucositis evaluation.

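### The only stated non-inferiority criterion sets the estimated effect against the 0.5-grade margin and names no confidence bound or test, which does not match the one-sided 0.025 level used to size the trial

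*Protocol article*

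**What the plan says.** The Statistical analysis section of the protocol article makes non-inferiority of the transcutaneous (TC) to the intraoral (IO) route the primary objective and states how it will be judged: "Non-inferiority will be assessed using the estimated treatment effect obtained from the longitudinal mixed-effects model and interpreted according to the prespecified non-inferiority margin", which is 0.5 WHO grade. The effect comes from a mixed-effects ordinal logistic model with group, time and their interaction, a participant random effect and three covariates.

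The margin and error rates are set under Sample size. There, "The non-inferiority margin was defined as Δ = 0.5 points on the WHO scale", and the calculation uses "a significance level (α) of 0.025 (one-tailed test) and a statistical power (1 - β) of 80" per cent. The method was a comparison of two means ("Calculations were performed using the ClinCalc platform to compare two independent means"). No SD and no numerical true difference are given.

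No confidence interval is mentioned anywhere in the article, and the Statistical analysis section does not repeat or refer to the 0.025 level.

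**The concern.** A one-sided 2.5% error rate exists only if the decision uses a test or a confidence limit at that level. The stated criterion has two ingredients, the estimated effect and the margin. Followed to the letter, it makes no allowance for sampling error: an estimate of 0.4 grade would pass however wide its interval.

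At stake is the trial's main conclusion. With about 24 evaluable patients per arm, an estimate well inside the margin can be compatible with a true loss larger than the margin. A TC route worse than the plan's own limit could then be reported as non-inferior. The trial is open-label and the treating team grades the outcome, so there is added reason to fix the rule unambiguously before any estimate is seen.

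**Working it through.** **Inputs**

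- Margin: 0.5 WHO grade (Sample size; repeated under Statistical analysis).
- One-sided level 0.025 and power 80% (Sample size): normal quantiles 1.960 and 0.842.
- 27 per group, 10% attrition (Sample size): 27 × 0.9 = 24.3, about 24 evaluable per arm.
- True difference: taken as 0. This is an assumption; the plan says only "assuming that transcutaneous infrared PBMT would demonstrate clinical efficacy comparable to intraoral red PBMT".
- SD of the WHO grade: not stated. It is back-solved below, then varied from 0.5 to 1.2 as an assumption.

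**Step 1. The plan's own sample size.** n per arm = 2 × SD² × (1.960 + 0.842)² / 0.5². With SD 0.61 this is 2 × 0.3721 × 7.85 / 0.25 = 23.4, so 24. Then 24 / 0.9 = 26.7, so 27 per arm and 54 in total. The stated size therefore fits a one-sided 0.025 test or bound if the SD was about 0.61. It cannot be confirmed, because the SD is not given.

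**Step 2. Implied standard error.** SE = 0.5 / (1.960 + 0.842) = 0.178 grade. With 24 per arm this corresponds to SD = 0.178 × √(24/2) = 0.618.

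**Step 3. Two readings of the criterion.** Let d be the true TC minus IO difference; a higher grade is worse.

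- Estimate only (literal reading): P(declare) = Φ((0.5 − d)/SE).
- Upper limit of the two-sided 95% interval below 0.5: P(declare) = Φ((0.5 − d)/SE − 1.96).

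At d = 0.5 the literal reading gives Φ(0) = 50% for any SD or sample size. The bound gives Φ(−1.96) = 2.5%.

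At d = 0.6 with SE 0.178, (0.5 − 0.6)/0.178 = −0.56. The literal reading gives Φ(−0.56) = 29% and the bound Φ(−2.52) = 0.6%.

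With 24 per arm, across assumed SDs (estimate only / bound):

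| SD | SE | d = 0.5 | d = 0.6 | d = 0.75 | Estimate must be below, to pass the bound |
|---|---|---|---|---|---|
| 0.5 | 0.144 | 50% / 2.5% | 24% / 0.4% | 4% / 0.01% | 0.22 |
| 0.618 | 0.178 | 50% / 2.5% | 29% / 0.6% | 8% / 0.04% | 0.15 |
| 0.8 | 0.231 | 50% / 2.5% | 33% / 0.8% | 14% / 0.12% | 0.05 |
| 1.0 | 0.289 | 50% / 2.5% | 36% / 1.1% | 19% / 0.24% | −0.07 |
| 1.2 | 0.346 | 50% / 2.5% | 39% / 1.2% | 24% / 0.37% | −0.18 |

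At the implied SE the two readings disagree for every estimate between about 0.15 (0.5 − 1.96 × 0.178) and 0.50 grade.

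**Step 4. Simulation.** In 200,000 simulated two-group comparisons of normal means, 24 per arm and a true difference of 0.5, the estimate-only rule passed 50.1% of the time at SD 0.618 and at SD 1.0. The bound passed 2.5% and 2.4%. This checks the formulas for a comparison of means, which is what the sample size assumes. It does not check the repeated-measures ordinal model.

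**Step 5. Scale.** All of these figures presuppose an estimate in WHO grades. The planned model yields a log-odds ratio, and with a group-by-time interaction the group coefficient refers to a reference time. A bound on that coefficient cannot be set against 0.5 grade without a conversion.

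**The case against.** The strongest reply is that the sentence does not say point estimate and does not say uncertainty is ignored. A confidence limit is also derived from the estimated effect. The Sample size section describes a one-tailed test at 0.025, and the analysis sentence refers back to the margin set there. Read together, the two sections most coherently imply a one-sided 2.5% bound that was left unnamed. This stands as far as intent goes. A reader might infer that the team has committed itself to the bare estimate, or that the trial has a 50% false non-inferiority rate. The documents do not support either inference; they show only that the written criterion leaves the bound out.

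A second reply is that an article may leave the interval and its level to a full protocol or analysis plan. That would hold if the article were silent. It is not: it states how non-inferiority will be judged, and what it states does not carry the error rate the trial was sized on.

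Third, the 50% is generic, true of any symmetric, centred estimate at any margin, and it presumes a grade-scale effect that the model does not directly give. Both points are correct and limit how the figure may be used. Likewise, a reader might take 29% against 0.6%, or the 0.15 to 0.50 zone, as properties of this trial. They rest on a back-solved SE and an assumed true difference of 0.

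The pilot label does not answer the point, since the plan sets a formal margin, level and power and makes non-inferiority its primary objective.

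**Conclusion.** The concern holds as a defect of the stated criterion. The only rule for the primary conclusion names no bound, level or test and so does not match the one-sided 0.025 level behind the 54 participants. Taken literally, and given an unbiased grade-scale estimate, false non-inferiority at the margin is about 50% instead of 2.5%; this part needs no SD. Beyond the margin the size depends on assumptions: 24% to 39% against 0.4% to 1.2% at a true deficit of 0.6 grade for SDs of 0.5 to 1.2. Whether a bound was intended cannot be settled from the article, and estimates for which the answer would decide the result are plausible in a trial of this size.

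**What to change.** Replace the criterion in the Statistical analysis section with wording to this effect:

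> Non-inferiority will be concluded only if the upper limit of the two-sided 95% confidence interval (one-sided 97.5%) for the TC minus IO difference in mean WHO grade is below 0.5. Otherwise non-inferiority will be reported as not shown, whatever the point estimate.

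Define that difference in the same place: a model-derived contrast in mean WHO grade, at one prespecified time point or averaged over a prespecified period. It can be obtained from the predicted category probabilities, with a bootstrap or delta-method interval. Make the change before any outcome comparison is seen.

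The cost is a few lines of text and a little more analysis work, with no extra data. Non-inferiority becomes harder to declare. With 24 per arm and a true difference of 0, the bound gives 80% power at SD 0.618, but 58% at SD 0.8 and 41% at SD 1.0. The 80% case is the requirement the sample size already assumes.

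### The 0.5-grade non-inferiority margin is set against an ordinal-logistic treatment effect that is in log-odds and varies with time; no conversion and no time or averaging window is named, so the rule cannot be applied as written

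*Protocol article*

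**What the plan says.** Three statements in the protocol article have to fit together.

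- **Margin and sizing (Sample size).** "The non-inferiority margin was defined as Δ = 0.5 points on the WHO scale". On the calculation: "Calculations were performed using the ClinCalc platform to compare two independent means". The error rate is one-sided 0.025, power is 80%, and the total is 54 after allowance for 10% attrition. Margin and sizing are therefore both in grade points, as a difference in means.
- **Primary model (Statistical analysis).** WHO grade is analysed by mixed-effects ordinal logistic regression. "The model will include treatment group, assessment time, and the treatment vs. time interaction as fixed effects". Participant is a random effect; total radiotherapy dose, tumour location and concomitant chemotherapy are covariates.
- **Decision rule (last sentence of Statistical analysis).** Non-inferiority rests on the "estimated treatment effect obtained from the longitudinal mixed-effects model and interpreted according to the prespecified non-inferiority margin of 0.5 WHO grade".

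The Primary outcome and Data collection sections name the WHO scale and grading at each clinical visit. Neither names a time point or a summary such as worst, mean or final grade.

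**The concern.** The margin is in grades and the model's treatment effect is in log-odds. With the interaction in the model there is also no single treatment effect: the log-odds ratio at time t is the group coefficient plus the interaction term at t. Because of the participant random effect, each of these is conditional on the participant rather than a population-average quantity.

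To apply the rule, someone must decide (a) how log-odds become grades and (b) at which time, or over which period, the arms are compared. The document fixes neither. This is the decision rule for the primary objective, and the Randomization and blinding section says that the treating team also grades the outcome, unblinded. If those two choices are made after grades by arm have been seen, they can settle the result.

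**Working it through.** **1. The scale on which the trial was sized.** For two means with true difference 0, n per arm = 2·SD²·(1.960 + 0.842)² / 0.5². The SD is not stated. An SD of about 0.61 gives 2 × 0.3721 × 7.849 / 0.25 = 23.4, so 24 per arm; 24 / 0.9 = 26.7, so 27 per arm and 54 in total. The stated total is thus consistent with a comparison of mean grades at that back-solved SD. The missing SD is a separate matter; what counts here is that 54 belongs to a mean-difference analysis.

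**2. What 0.5 grade means on the model's scale.** The document gives no grade distribution, so those below are assumptions. Under proportional odds, ignoring the random effect,

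P(Y > k | TC) = expit{ logit P(Y > k | IO) + β }, and mean grade = sum over k = 0 to 3 of P(Y > k).

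Worked case, IO grades 0 to 4 in 20/35/30/12/3%:

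- IO exceedance probabilities are 0.80, 0.45, 0.15 and 0.03; the mean is 1.43.
- At β = 0.5 they become 0.868, 0.574, 0.225 and 0.049, which sum to 1.72. The difference is 0.29 grade.
- At β = 0.867 (odds ratio 2.38) they become 0.905, 0.661, 0.296 and 0.069, which sum to 1.93. The difference is 0.50 grade.

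All four assumed distributions:

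| IO grades 0–4 (%) | Mean | Log-OR equal to +0.5 grade | OR | Grade difference if log-OR = 0.5 |
|---|---|---|---|---|
| 70/25/5/0/0 | 0.35 | 1.50 | 4.50 | 0.14 |
| 20/35/30/12/3 | 1.43 | 0.87 | 2.38 | 0.29 |
| 5/15/40/30/10 | 2.25 | 0.95 | 2.60 | 0.27 |
| 0/20/60/20/0 | 2.00 | 1.58 | 4.87 | 0.16 |

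**3. Sensitivity to the random effect.** A second assumed set, with every grade occupied and a normal participant intercept:

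| IO mean grade | OR equal to +0.5 grade, intercept SD 0 | SD 1 | SD 2 |
|---|---|---|---|
| 0.14 | 6.2 | 7.5 | 12.8 |
| 0.44 | 3.1 | 3.6 | 5.4 |
| 1.28 | 2.2 | 2.5 | 3.4 |
| 2.05 | 2.3 | 2.6 | 3.6 |

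A log-odds ratio of 0.5 here equals 0.06 to 0.31 grade. The conversion depends on the grade distribution, which changes through radiotherapy, and on the between-participant variance. No constant links the two scales.

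**4. Time.** Thirty to 35 fractions at five a week is 6 to 7 weeks. Three sessions a week, with grading at each, gives 18 to 21 occasions. The interaction allows a different arm contrast at each. As an assumed example, no difference for two weeks and 0.5 grade afterwards averages 0.5 × 4/6 = 0.33 over six weeks or 0.5 × 5/7 = 0.36 over seven. The late-period contrast would be 0.5 in the same patients. The document does not say which of these is to be compared with the margin.

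**The case against.** The strongest reply is that the model is able to supply what the rule needs. It gives predicted grade probabilities, hence a mean grade per arm and a difference in grades. The text says that the effect is interpreted against the margin; it does not say that a raw coefficient will be compared with 0.5. Standardisation after the model and construction of the interval are commonly left to an analysis plan, which is not shown.

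Much of this stands. A reader might infer that the stated model cannot produce a grade difference; that is too strong, and the fix below relies on the opposite. What remains is that the article does state margin, model and the rule linking them, and as stated they are on different scales with no contrast named. That is a mismatch in the text, not merely an omitted detail.

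Other inferences are tempting and unsupported:

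- *That the treatment coefficient is the contrast at the start of radiotherapy.* This depends on how time is coded, and the coding is not stated. With centred time it would be a mid-course effect.
- *That averaging all visits raises the false-claim rate well above 2.5%.* If the all-visit average is the quantity of interest, a true average of 0.33 to 0.36 lies inside the margin and a non-inferiority claim is correct. Any inflation figure presumes that a late window is the right target, and needs an SD that the document does not give.
- *That early visits must be left out.* The Discussion says "These therapeutic effects typically manifest between the second and third weeks of RT", but this is about when the benefit of PBMT appears in published reviews, not when the two routes would diverge. In a prevention trial, differences in onset may matter.
- *That the random-effects structure understates the error.* The text says only that participant is a random effect. Whether a random slope is needed depends on a slope variance that the document does not give.

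**Conclusion.** The rule cannot be applied as written. Margin and sample size are on the mean-grade scale; the named treatment effect is a participant-conditional log-odds ratio that varies with time; and the document gives neither a conversion nor a time or averaging window.

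The odds-ratio range of about 2.4 to 4.9 for 0.5 grade, and the 0.14 to 0.29 grade for a log-odds ratio of 0.5, rest on assumed grade distributions without a random effect. The two highest odds ratios come from distributions with empty grades; the two with all grades occupied give 2.4 and 2.6. Other assumptions give 2.2 to 12.8. These figures are illustrative. The conclusion that no fixed conversion exists does not depend on which are chosen.

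This should be corrected before any outcome data are compared by arm. It does not show that the ordinal model is the wrong model, that a particular window is right, or that the error rate rises by any stated amount.

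**What to change.** Replace the last sentence of Statistical analysis with one prespecified contrast, for example:

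*The primary effect is the TC minus IO difference in mean WHO grade [at a named time / averaged over a named period of radiotherapy]. It is obtained by standardising the ordinal model's predicted grade probabilities over all participants, including the random effect, with a two-sided 95% confidence interval from a participant-level bootstrap. TC is declared non-inferior if the upper limit is below 0.5.*

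The sponsor should choose and justify the time or period before any outcome data are compared by arm. The two-sided 95% limit matches the one-sided 0.025 in Sample size.

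A linear mixed model on the grade is a simpler acceptable route, since its contrast is already in grades; it still needs the named time or period. Restating and justifying the margin as an odds ratio is a third option, but the sample size would then have to be redone on that scale.

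Cost of the first two routes: a wording change and a little more analysis work, with no new data. The standardisation and bootstrap may have to be run outside Jamovi, the only software named.
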